### Outcome assessments

Participants will undergo reassessment at various intervals following enrolment, as outlined in
Table 3. Examinations will be conducted similarly to the baseline assessment. Adherence to treatment and symptoms, including side effects, will be queried and recorded at each follow-up. Trial medication adherence will be monitored by weighing eye drop bottles at specified follow-ups, with resupply provided as necessary. Visual acuity will be measured at each visit, with BSCVA assessed at the three-month follow-up (primary outcome measure). Quality of life questionnaires will be repeated at the final three-month follow-up. Slit-lamp examination and corneal photography will be performed at each visit. In vivo confocal microscopy will be repeated at specified intervals to assess fungal hyphae resolution. If the ulcer has not healed at the one-week follow-up, re-scraping for repeat culture will be conducted. Appointment cards will be provided for follow-ups, and transport costs will be covered for outpatient participants.

**Table 3. T3:** Baseline and follow-up assessment components.

Assessment Item	Baseline	Day 2	Day 7	Day 14	Day 21	Day 60	Day 90
History / Baseline questionnaire	X						
Check treatment adherence		X	X	X	X	X	X
Check for side effects		X	X	X	X	X	X
Visual Acuity – Presenting	X	X	X	X	X	X	X
Visual Acuity – BSCVA	X						X
Contrast Sensitivity	X						X
Slit-lamp Examination	X	X	X	X	X	X	X
Cornea Photography	X	X	X	X	X	X	X
*In vivo* confocal microscopy	X		X	X	X		
Cornea samples (Microbiology/PCR)	X		X				
Quality of Life Tools	X						X

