Secondary outcomes listed in
Table 4 will be analyzed using regression models appropriate for the data type, adjusting for any baseline imbalances. 

**Table 4. T4:** Secondary Outcome Measures that will be investigated as part of the trial, together with analysis details.

Secondary outcome measure	Details
Three-week BSCVA	We will analyze the secondary outcome of three-week Best Spectacle-Corrected Visual Acuity (BSCVA) in logMAR using the same methodology applied to the primary analysis of the primary outcome. The three-week BSCVA assessment will include values recorded between 18 days and 5 weeks, with the closest value to 3 weeks being selected.
Presenting VA by Peek	The presenting visual acuity (VA) assessed using Peek Acuity, with and without pinhole, will also be analyzed as a secondary outcome at three months. This measure will be particularly relevant if reliable BSCVA readings cannot be obtained at three months (e.g., if patients do not attend the clinic and at-home visual acuity testing is required). This analysis will follow the same approach as the primary analysis of the primary outcome. A sensitivity analysis, incorporating data from participants lost to follow-up, will use the most recent recorded observation of this variable.
Scar/infiltrate size at 1 week, 3 weeks and 3 months by slit lamp examination.	For scar or infiltrate dimensions, the geometric mean of the two principal axes (in mm) will serve as the outcome variable at one week, three weeks, and three months. The scar size, observed via slit lamp, will be compared between treatment groups at each time point using linear regression. This will include treatment arm and baseline infiltrate/scar size as predefined covariates, controlling for baseline differences.

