Time to full epithelial healing (slit lamp examination by ophthalmic clinician)	The time to re-epithelialization will be calculated as the midpoint between the last review showing an epithelial defect (ED) and the subsequent review where no ED is observed. Fluorescein staining covering an area smaller than 0.5 mm will be considered indicative of a resolved ED, given the challenge of distinguishing smaller defects from pooling in healed areas. Time-to-healing analysis will utilize Cox proportional hazards regression, with treatment group as the primary predictor and baseline ED size (geometric mean in mm) included as a covariate. Survival curves for treatment groups will be plotted using Kaplan-Meier analysis up to the three-month endpoint. The proportional hazards assumption will be tested by stratifying baseline ED size into quartiles. If this assumption is not met, stratified results will be reported. Treatment failure (defined as an ED larger than 0.5 mm at the three-month review) will be compared between groups using Fisher’s exact test.
Rate of healing	The rate of ulcer size reduction will be evaluated by measuring changes in ED size over time intervals (1 week to 3 weeks, and 3 weeks to 3 months) and dividing by the number of days, producing a rate (mm/day). This will be analyzed using Cox regression.
Microbiological cure	For patients with persistent corneal ulcers (defined by ED presence) at day 7, a repeat corneal scrape and microbiological tests will be conducted. Microbiological cure at day 7 will be defined as the absence of growth on culture. Cure rates will be compared between treatment arms using logistic regression, adjusting for organism type (e.g., *Aspergillus spp.*, *Fusarium spp.*, or other).
Ulcer depth at 1 week and 3 weeks (slit lamp examination by ophthalmic clinician).	Depth of corneal ulcers (expressed as a percentage of healthy cornea thickness) will be compared between treatment groups at one week and three weeks. This analysis will adjust for baseline ulcer depth using linear regression.
Hypopyon height at 1 and 3 weeks, (slit lamp examination by ophthalmic clinician)	Hypopyon height (in mm) at one and three weeks will be compared between groups, adjusting for baseline height using linear regression.

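### Rate of healing in mm/day is assigned to Cox regression over intervals that skip the first week; the model does not suit the variable, and the intervals cannot separate early healers from non-responders

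*Protocol article*

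**What the plan says.** In the protocol article, the Rate of healing row of Table 4 (Analysis plan) builds the variable by "measuring changes in ED size over time intervals (1 week to 3 weeks, and 3 weeks to 3 months" and then by "dividing by the number of days, producing a rate (mm/day). This will be analyzed using Cox regression". The row names no event, time origin or censoring rule. It gives no interval from baseline to week 1 and no rule for eyes already healed at week 1.

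The sentence introducing Table 4 says that the secondary outcomes "will be analyzed using regression models appropriate for the data type, adjusting for any baseline imbalances". The other continuous slit-lamp outcomes follow that rule. For example: "Hypopyon height (in mm) at one and three weeks will be compared between groups, adjusting for baseline height using linear regression". Scar or infiltrate size and ulcer depth are also assigned linear regression.

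Time to full epithelial healing is a separate row with its own Cox model, "with treatment group as the primary predictor and baseline ED size (geometric mean in mm) included as a covariate". In that row, "Fluorescein staining covering an area smaller than 0.5 mm will be considered indicative of a resolved ED". Its diagnostic is this: "The proportional hazards assumption will be tested by stratifying baseline ED size into quartiles". If the assumption fails, stratified results are to be reported.

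The Outcome assessments section allows for healing within a week: "If the ulcer has not healed at the one-week follow-up, re-scraping for repeat culture will be conducted".

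**The concern.** There are two faults in the rate row and a lesser one in the time-to-healing row.

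- **Model.** Cox regression estimates the effect of treatment on the hazard of an event over time. A rate in mm/day is not a time to anything. It is zero when the defect does not change and negative when it enlarges, and a survival time cannot be negative. Worsening is expected in some eyes: the Introduction reports progression to perforation or loss of vision in up to 30% of patients even with natamycin.
- **Intervals.** An eye that closes in the first week has no defect left to shrink in either planned interval. The best possible course and a complete lack of response receive the same score. An arm that moves more eyes into early healing gains nothing on this measure and may lose.
- **Proportional hazards.** The stated check and its fallback concern the baseline covariate. The quantity to be reported is the treatment hazard ratio, and no check of its constancy is described.

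At stake is a reported secondary result that could be uninterpretable or, under some conditions, point the wrong way.

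**Working it through.** **The plan's own figures.** The plan gives no figure for either healing outcome. Its only design calculation is for the primary outcome: SD 0.62, difference 0.2 logMAR, two-sided alpha 0.0492, power 80%. This gives n = 2 × 0.62² × (1.967 + 0.842)² / 0.2² = 151.6, so 152 per arm and 304 in total. Then 304/0.85 = 357.6, so 358. Both stated figures reproduce, and neither depends on the point made here.

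**Step 1: the stated definition applied to example eyes.** The visits are at days 7, 21 and 90, so the planned intervals last 14 and 69 days. The ED sizes are invented for illustration.

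| ED in mm at baseline, week 1, week 3, month 3 | Baseline to week 1 (not planned) | Week 1 to 3 | Week 3 to month 3 |
|---|---|---|---|
| 3, 0, 0, 0 | 3/7 = 0.43 | 0 | 0 |
| 3, 2, 0, 0 | 1/7 = 0.14 | 2/14 = 0.14 | 0 |
| 6, 5, 2, 0 | 1/7 = 0.14 | 3/14 = 0.21 | 2/69 = 0.029 |
| 3, 3, 3, 3 | 0 | 0 | 0 |

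The first and last eyes are indistinguishable on the planned measure. Only the omitted interval separates them. This needs no assumption about healing speed.

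**Step 2: whether the ranking of the arms can reverse.** This does need assumptions, because the documents give no ED sizes or healing speeds. Assumed: baseline ED lognormal with median 3.5 mm and log-SD 0.4, limited to 1–9 mm; linear shrinkage; speed lognormal with log-SD 0.8; ED below 0.5 mm counted as healed, as the plan states. The faster arm heals 1.67 times as fast. The third decimal shifts slightly with how the size limits are imposed.

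| Median speed, control v faster arm (mm/day) | Week 1 to 3 rate, control v faster arm | Order |
|---|---|---|
| 0.05 v 0.083 | 0.060 v 0.081 | correct |
| 0.08 v 0.133 | 0.080 v 0.094 | correct |
| 0.10 v 0.167 | 0.087 v 0.096 | correct |
| 0.12 v 0.20 | 0.092 v 0.095 | correct |
| 0.15 v 0.25 | 0.096 v 0.091 | reversed, by 0.005/0.096 = 5% |

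At 0.15 v 0.25, 13% v 29% of eyes are healed by day 7, and the baseline to week 1 rate is 0.19 v 0.28 mm/day, in the correct order. The week 3 to month 3 rate is 0.015 v 0.008, reversed. That rate stays reversed in every row of the table.

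A second grid used control speeds from 0.05 to 0.30 mm/day and a 1.5-fold faster arm. The week 3 to month 3 rate was reversed in all six scenarios. The week 1 to 3 rate was reversed from 0.15 mm/day upward and correct at 0.10 or below. Rates measured from baseline to week 1 and to week 3 kept the correct order throughout.

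The reason is simple. If nearly all eyes are healed by month 3, the last rate is close to the ED remaining at week 3 divided by 69, so a better arm with less defect left scores lower.

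**Step 3: what Cox regression returns.** Assumed: baseline median about 3 mm, median speed 0.2 mm/day, one arm 1.3 times faster, 2,000 eyes per arm.

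- Cox on time to healing: hazard ratio 1.25, correctly favouring the faster arm.
- Cox with the true rate entered as the time: 0.74, the opposite direction on the usual reading.
- Cox on the planned week 1 to 3 rate, with a negligible constant added to the zeros: 1.02, with 33% of eyes at exactly zero.

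**Step 4: the proportional hazards check.** Splitting baseline ED size into quartiles asks whether that covariate can be handled by one proportional term. The treatment hazard ratio could change over follow-up within every quartile, and neither the check nor quartile-stratified reporting would show it.

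**The case against.** The best defence is that little depends on this row. Rate of healing is absent from the abstract, from the Objective section and from the key secondary outcomes in Table 5. All three name healing time instead, and that analysis counts from baseline with visits at days 2, 7, 14 and 21. A reader might infer that a first-week benefit would be lost to the trial. It would not be, because the time-to-healing row captures it. This stands, and it limits the severity.

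The article also does not say how eyes healed at week 1 enter the analysis; a score of zero is the result of the stated arithmetic, not a written rule. They might be left out, and at 0.15 v 0.25 mm/day that restores the correct order in week 1 to 3 (0.110 v 0.126). But leaving them out selects eyes on something that happened after randomisation and that treatment may affect, so it exchanges one problem for another.

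A reader might also infer that both planned rates will show a better treatment as worse. The documents do not support that for week 1 to 3. The Treatment review section says that topical therapy is often needed for 4–6 weeks. If epithelial closure took as long, the median speed would be about (3.5 − 0.5)/42 = 0.07 to 3.0/28 = 0.11 mm/day, where that rate keeps the correct order. Duration of therapy is not closure time, so this is only a rough guide. Nor is it right that the Cox analysis cannot be run. Software will return a number once zeros and negatives are somehow handled, but the number lacks meaning.

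On proportional hazards, stratifying on baseline size is a recognised remedy if that covariate is the problem. Kaplan-Meier curves by arm are planned, as is Fisher's exact test of failure at three months. A SAP could add a treatment check. To say that proportionality for treatment will never be examined would go beyond the text. What stands is that the article states one check and one fallback, and neither concerns treatment.

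**Conclusion.** The concern holds as a secondary-outcome error of moderate to low severity.

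- **Certain from the text:** Cox regression does not suit a mm/day rate. It conflicts with the article's own rule of matching the model to the data type and with the linear regression used for the other continuous slit-lamp outcomes.
- **Certain by arithmetic, barring a recurrent defect:** an eye healed by day 7 scores 0 in both planned intervals, the same as an unchanged eye.
- **Dependent on assumed speeds:** the week 3 to month 3 rate ranked the faster arm as slower in all scenarios tried; the week 1 to 3 rate did so only from about 0.15 mm/day in the control arm.
- **Weaker:** the stated proportional hazards check omits treatment, although an unseen SAP may supply one.

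The primary BSCVA analysis and the sample size of 304 evaluable and 358 enrolled are not touched.

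**What to change.** In the Rate of healing row of Table 4, define two rates for all randomised eyes with data: (baseline ED − week 1 ED)/days and (baseline ED − week 3 ED)/days. Analyse each by linear regression on arm, baseline ED size and centre; centre belongs in the model because each has its own randomisation sequence. A small downside is that the week 3 rate gives eyes of equal baseline size the same score whenever they heal before week 3. The time-to-healing analysis covers that difference.

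In the Time to full epithelial healing row, add a check of proportional hazards for treatment, by Schoenfeld residuals or an arm-by-time term. State that if it fails, the difference in restricted mean time to healing to day 90 will be reported.

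The cost is the rewording of two table rows before analysis. Slit-lamp examination is already scheduled at baseline and at every visit in Table 3, so no new measurement is needed.

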1. Acute MK characterised by: • Corneal epithelial ulceration >1mm diameter • Corneal stromal infiltrate • Acute inflammation: e.g. conjunctival injection, anterior chamber inflammatory cells, hypopyon. 2. Filamentous fungal hyphae visualised on smear microscopy and/or *in vivo* confocal microscopy. 3. Agree to be randomised to either treatment arm and are able to give informed consent 4. Agree to be followed up at 2 days, 1 week, 2 weeks, 3 weeks, 2 months and 3 months 5. Adults (18 years and older)	1. Unwilling/unable to participate in trial and/or attend follow-up 2. Aged less than 18 years 3. Pregnancy: self-reported, or by urine hCG pregnancy test if uncertain. 4. Breast feeding: self-reported 5. No light perception in the affected eye 6. Fellow eye visual acuity <6/60 7. Acanthamoebic infection visualised by smear microscopy or IVCM 8. Clinical evidence of herpetic keratitis 9. Known allergy to study medication (including preservatives) 10. Previous keratoplasty in the affected eye 11. Bilateral corneal ulcers 12. Nationals of another country 13. Very severe ulcers warranting immediate evisceration or conjunctival flap 14. Endophthalmitis

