### Non-pharmacological treatment

Surgical interventions, performed by supervising consultant ophthalmologists, may include bandage contact lens insertion, tissue glue and patch application, or conjunctival flaps to manage small perforations or non-healing ulcers. Corneal transplant is not available in Uganda or Tanzania.

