### Analysis plan

An intention-to-treat (ITT) approach will be used, analyzing all data based on the assigned randomisation group, regardless of adherence to the treatment protocol. Analyses will follow CONSORT guidelines for non-inferiority trials
^
35
^, and a flowchart will summarize recruitment, randomisation, and follow-up by treatment arm. Baseline characteristics will also be summarized. Details of the SPIRIT checklist are provided as Extended Data and available online (see Data Availability Statement). 

**
*Primary outcome analysis – unadjusted*
**

The primary outcome (BSCVA at 3 months) will be analyzed using linear regression, including baseline BSCVA and treatment arm as covariates. Mixed fungal and bacterial infections identified at baseline will be excluded from the primary analysis. We will use our alpha of 0.0492 to test the null hypotheses at 0.0492 significance. Significance will be assessed using a two-tailed test at 0.0492 level for assessing superiority.

**
*Primary outcome analysis – adjusted*
**

If baseline covariate imbalances occur between treatment arms, adjusted analyses will be conducted to ensure treatment effects are not confounded by these differences. This is particularly important if natamycin + chlorhexidine has a better outcome than natamycin, as the adjusted treatment effects may account for this observed imbalance whilst the unadjusted analyses may not. Sensitivity analyses will allow us to show that any observed positive treatment effect is not solely explained by imbalances at baseline in any of the covariates.

**
*Secondary analyses of the primary outcome*
**

- Per-Protocol Analysis: Re-analysis will be conducted excluding participants with significant deviations, poor adherence (<50%), or mixed/non-fungal infections. 

- Mixed Infections: Secondary analyses will include mixed infections using the same methodology as the primary analysis. 

- Sensitivity Analyses: Missing data will be addressed through multiple imputation or non-random missing data models if necessary. Additional sensitivity analyses will assess outcomes in subgroups such as those with severe vision loss, corneal perforation, or therapeutic keratoplasty. 

**
*Analysis of other determinants for success*
**

Logistic regression models will identify factors associated with poor outcomes (BSCVA >1.0 logMAR), adjusting for trial arm. Multivariate models will refine predictors based on likelihood ratio tests. 

**
*Secondary outcome analysis*
**

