Key eligibility criteria	1. Acute MK characterised by: • Corneal epithelial ulceration >1mm diameter • Corneal stromal infiltrate • Acute inflammation: e.g. conjunctival injection, anterior chamber inflammatory cells, hypopyon. 2. Filamentous fungal hyphae visualised on smear microscopy and/or *in vivo* confocal microscopy. 3. Agree to be randomised to either treatment arm and able to give informed consent 4. Agree to be followed up at 2 days, 1 week, 2 weeks, 3 weeks, 2 months and 3 months 5. Adults (18 years and older)
Study type	Randomised controlled trial
Date of first enrolment	12 May 2021
Target sample size	358
Recruitment status	Recruiting
Primary outcome(s)	Best Spectacle Corrected Visual Acuity (BSCVA) at 3 months by a trial certified optometrist
Key secondary outcomes	1. Time to full epithelial healing (slit lamp examination by ophthalmic clinician). 2. Pin-hole visual acuity in logMAR at 3 months, trial-certified optometrist 3. Scar/infiltrate size at 1 week, 3 weeks and 3 months (slit lamp examination by ophthalmic clinician). 4. Ulcer depth at 1 week and 3 weeks (slit lamp examination by ophthalmic clinician). 5. Hypopyon height at 1 and 3 weeks, (slit lamp examination by ophthalmic clinician). 6. Perforation and/or TPK by three months (slit lamp examination by ophthalmic clinician). 7. Positive culture rate at 1 week 8. Ocular adverse effects at each follow up visit (Day 2, Day 7, Day 14, 3 weeks, 2 months, 3 months), slit lamp examination by ophthalmic clinician. 9. Quality of life (QoL) assessed using: EQ-5D, WHO/PBD-VF20, WHOQOL-BREF (comparison between baseline and QoL measures at 3 months) 10. Cost-effectiveness analysis, using EQ-5D data from 3 months and direct cost data. 11. Drug adherence at each follow up visit (Day 2, Day 7, Day 14, 3 weeks, 2 months, 3 months) whilst the patient is using study medications.

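### Day-7 microbiological cure is defined only for eyes not healed by day 7, so on the natural reading the arms are compared in a group that treatment can change

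*Protocol article*

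**What the plan says.** Under Outcome assessments, the day-7 re-culture is conditional: "If the ulcer has not healed at the one-week follow-up, re-scraping for repeat culture will be conducted". The Microbiological cure row of Table 4 repeats the restriction, "For patients with persistent corneal ulcers (defined by ED presence) at day 7, a repeat corneal scrape and microbiological tests will be conducted", then defines the outcome, "Microbiological cure at day 7 will be defined as the absence of growth on culture", and names the analysis, "Cure rates will be compared between treatment arms using logistic regression, adjusting for organism type". It gives no value to an eye that has healed and was not scraped, and no denominator.

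Table 5 lists the outcome as "Positive culture rate at 1 week", also without a denominator. The Objective section names day-7 re-culture positivity among the secondary clinical outcomes.

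For entry to the randomised stage, Table 1 requires "Filamentous fungal hyphae visualised on smear microscopy and/or" in vivo confocal microscopy (IVCM). A positive culture is not required.

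On the primary outcome, the Analysis plan adds: "Additional sensitivity analyses will assess outcomes in subgroups such as those with severe vision loss, corneal perforation, or therapeutic keratoplasty". Table 4 treats perforation and therapeutic keratoplasty as outcomes up to three months. Non-pharmacological treatment states: "Corneal transplant is not available in Uganda or Tanzania". Treatment review, the Analysis plan and Table 4 nevertheless provide for keratoplasty.

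**The concern.** Whether an eye is still open at day 7 is known only after treatment has started, and time to healing is itself a trial outcome. If one arm closes more ulcers in the first week, its best responders leave the day-7 comparison and the eyes left behind are on average worse. Adjusting for organism type does not restore the balance.

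Two features of the definition add to this. A patient enrolled on smear or IVCM whose baseline culture grew nothing counts as cured if the day-7 culture is also negative. Such a patient also has no evident category in a model adjusted for organism type. And growth is not restricted to fungus, although Table 2 has baseline samples inoculated onto blood and chocolate agar as well as Sabouraud, and the Abstract describes chlorhexidine as both antibacterial and antifungal.

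At stake is the reading of a named secondary outcome. The trial could report too small a culture benefit, or an apparent disadvantage, for the arm that heals faster, or flatter the arm that heals more slowly.

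**Working it through.** **The plan's own figures.** The article gives no figure for this outcome. Its sample size for the primary outcome reproduces: SD 0.62, difference 0.2 logMAR, two-sided alpha 0.0492 and 80% power give 152 per arm, 304 in total, and 304/0.85 = 357.6, rounded up to 358. That is sound but does not bear on this point.

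**Can treatment change the selection?** The Introduction reports that in the Nepal trial patients on chlorhexidine alone healed 39% more slowly than those on natamycin. So the choice of topical agent can alter healing speed. The article does not say in which direction the combination would act.

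**Size, on assumed inputs.** Let severity U be standard normal and T = 1 for the combination.

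- Healed by day 7: logit = a − U + log(OR_heal)·T, with a set so that 5%, 15% or 30% of controls heal.
- Culture-positive if open: logit = c + U + log(OR_cult)·T, with c set so that 30% of open control ulcers are positive.

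Both slopes, the healed proportions and the 30% are assumptions. The table gives cure in the combination minus control, in percentage points, for 5% / 15% / 30% of controls healed. The composite counts healed eyes as cured among all randomised.

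| OR_heal | OR_cult | Open ulcers only | Composite, all randomised |
|---|---|---|---|
| 1 | 1 | 0.0 / 0.0 / 0.0 | 0.0 / 0.0 / 0.0 |
| 2 | 1 | −0.6 / −1.3 / −1.9 | +0.7 / +1.8 / +2.9 |
| 3 | 1 | −1.1 / −2.2 / −3.2 | +1.4 / +3.3 / +5.0 |
| 0.5 | 1 | +0.3 / +0.9 / +1.4 | −0.4 / −1.1 / −2.1 |
| 1 | 0.7 | +6.0 / +6.0 / +6.1 | +5.7 / +5.1 / +4.2 |
| 2 | 0.7 | +5.5 / +4.9 / +4.4 | +6.2 / +6.5 / +6.5 |

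The last two rows isolate the selection. With the same effect on culture, faster healing lowers the open-ulcer difference by 0.5, 1.1 and 1.7 points.

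**Against sampling error.** If all 358/2 = 179 per arm were scraped and 30% were positive, the standard error of the difference would be √(2 × 0.30 × 0.70/179) = 0.048, or 4.8 points, and larger with fewer scraped. The distortions above are below one standard error.

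**An extreme case.** Let 15% and 30% heal, with 25.5% of all randomised positive in both arms. Among scraped eyes this reads 0.255/0.85 = 30.0% against 0.255/0.70 = 36.4%, an odds ratio of (0.364/0.636)/(0.300/0.700) = 1.34 against the combination. But open and negative eyes are then 85 − 25.5 = 59.5% and 70 − 25.5 = 44.5%, so every additional closure comes from culture-negative eyes. This is perfect selection and not a likely size.

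**Never-positive patients.** If a fraction f of the analysed eyes grew nothing at baseline and stay negative, a difference d among the others reads as (1 − f)·d. Baseline culture status precedes treatment and should balance between arms, so this dilutes the contrast and does not select on a result of treatment.

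**Subgroups.** Table 1 excludes previous keratoplasty in the affected eye, so a keratoplasty subgroup can form only after randomisation. Perforation is mostly a follow-up event by Table 4, although baseline perforation is not a listed exclusion.

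**The case against.** A reader might infer that the article proves a biased analysis. It does not. It restricts who is scraped but states no denominator, and the Analysis plan applies intention-to-treat to all data. A condensed article may leave the analysis population to a fuller document, and healed eyes could be counted as cured there. This stands as far as it goes. Against it, cure is defined by the result of a culture that healed eyes do not have, so the text as written gives them no value.

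It can also be said that the effect is small. Treatment review describes antifungal responses as slow, which suggests few closures by day 7, and with a real effect on culture the open-ulcer comparison in the model still shows most of it. Both points stand, and they limit the size of the concern.

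The strongest objection concerns the remedy. Counting healed eyes as negative credits healing as microbiological success: in the model, with no effect on culture, the composite favours the faster-healing arm by 0.7 to 5.0 points. This too stands. The choice is between estimands, so the result must be labelled a composite.

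A reader might go further on the subgroups and say that the arms will be tested within them, or that the keratoplasty subgroup will be empty. The sentence is a loose list of sensitivity analyses that does not specify tests between arms, and the article contradicts itself on whether keratoplasty can occur.

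**Conclusion.** The point holds in a limited form. Followed as written, the day-7 culture comparison depends on healing, which treatment can affect, so it is not a randomised comparison and may understate or reverse a benefit of the faster-healing arm. That rests on the natural but unstated reading that only scraped eyes are analysed.

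The size cannot be fixed from the article. In the model it is −0.6 to −3.2 points for healing odds ratios of 2 to 3 with no effect on culture, and zero if treatment does not affect healing. To say that the analysis will show harm when the combination works would go beyond what the documents support.

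The cure definition has a separate, diluting fault in counting never-positive patients as cured, and it leaves bacterial growth undistinguished from fungal growth. The perforation and keratoplasty subgroups are at most descriptive. The primary comparison of visual acuity is conditioned on none of these events and is not affected.

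**What to change.** - **Population:** all randomised patients with a positive baseline fungal culture. The scrape is taken in Stage 1, before randomisation, so this does not select on treatment even when the result arrives later.
- **Outcome:** healed, or no fungal growth on culture, at day 7. Call it a composite, since it credits healing.
- **Model:** logistic regression by arm, adjusted for organism type and site.
- **Sensitivity:** vary the assumption that healed eyes are culture-negative.
- **Scraped-only rate:** report by arm as descriptive, beside the proportion healed by day 7.
- **Perforation and keratoplasty subgroups:** report descriptively and state that they are not randomised comparisons.
- **Availability of keratoplasty:** reconcile Non-pharmacological treatment with Treatment review, the Analysis plan and Table 4.

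The cost is wording; the data are already to be collected. The downsides are a smaller denominator and reliance on the assumption about healed eyes, which the sensitivity analysis exposes.
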